## 1. Introduction

The excitability of hypoglossal motoneurons innervating the genioglossus muscle, the main tongue protruder, is markedly suppressed during sleep in both healthy subjects and patients with obstructive sleep apnea (OSA) [1]. However, during wakefulness, apneic events hardly ever occur, regardless of the presence or absence of such episodes during sleep, because the genioglossus muscle reflectively augments its activity as needed to maintain the tongue in position to protect the upper airway patency [2]. Based on this phenomenon, we hypothesized that OSA could be alleviated if the resting tongue position during wakefulness can be maintained during sleep independently of genioglossus muscle activity [3].

In exploratory studies, we demonstrated that the maintenance of resting tongue position by continuous tongue suction improved OSA [3,4]. However, in subsequent trials, we also experienced treatment failure with a larger tongue; although the tongue appeared to be held throughout the night by tongue suction, the device likely allowed for the tongue base to collapse. This could indicate that not only maintaining resting tongue position per se, but also additional tongue protrusion, might mitigate tongue collapse more efficiently in OSA patients, who generally have larger tongues in comparison with non-OSA people [5,6,7,8]. Accordingly, the objective of this study is to test the following hypothesis (Figure 1); Compared with no control of tongue position, holding the tongue in a protruded position and in its resting position will improve the abnormal breathing events, with superior effects being achieved by the former in OSA patients. We designed a randomized controlled trial (RCT) to investigate the effects of controlling tongue position using a newly developed tongue position retainer (TPR) on upper airway patency in OSA during intravenous sedation. Our concept may lead to the development of different approaches to continuous positive airway pressure (CPAP) and mandibular advancement devices for OSA.

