### 2.5. Sample Size and Allocation Concealment Mechanism

In a previous study that evaluated the effect of tongue protrusion using a tongue-stabilizing device on the severity of OSA, Apnea Hypopnea Index (AHI) improved from 21.8 ± 8.6/h to 9.3 ± 5.8/h [18]. This indicates that, if intervention B is applied to a participant, there should be no change in AHI. Therefore, our null hypothesis is that the mean AHI was not different between intervention A (μ1) and intervention B (μ2) (i.e., μ1 = μ2), whereas the alternative hypothesis is that the mean AHI of intervention B is greater than that of intervention A (i.e., μ1 < μ2). The effect size (Δ0) and the power (i.e., 1-β) should be calculated with the following formula: Δ0 = (μ1 − μ2)/σ, 1 − β = Pr{t0 < −t(φ, 2α)}, φ = n1 + n2 − 2, where σ is the population standard deviation, β is the Type II error, φ is the degree of freedom, α is the Type I error set at 0.05, n1 is the number of subjects with intervention A, and n2 is the number of subjects with intervention B. Statistically, n1 and n2 are assumed to be equal (i.e., n1 = n2) to each other and 1-β is set at 0.80. Consequently, each intervention group needs 9 participants (i.e., 18 participants for both groups). If the drop-out rate is set rather high, at 30%, the study needs 25.7 samples; thus, a total of 26 participants will be required to test the hypothesis.

These 26 participants are to be randomized by creating a computer-generated randomization list using the permuted block method (Mujinwari, https://mujinwari.biz, Iruka-system, Tokyo, Japan: accessed on 28 May 2023) with random block sizes of two or four, stratified by body mass index (<25 kg/m^2^ or 25 kg/m^2^≤). Consequently, participants will be assigned random numbers based on consecutive enrollment into either sequence AB or sequence BA, which provides an approximately one-to-one ratio for the number of subjects in the two sequences.

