### 2.7. Study Outcome

#### 2.7.1. Primary Outcome

Since this study will be performed under intravenous sedation, and not during sleep, definitions of apnea and hypopnea as alternatives to AHI and REI that occur during sleep need to be prepared for scoring abnormal breathing. In other words, definitions for an intravenous sedation study as an alternative to AHI and REI and other variables for studies during sleep will more reasonably reflect the effects of the intervention on upper airway patency during intravenous sedation, as described in our previous report [20]. Abnormal breathing under intravenous sedation is to be predetermined by OCST based on five expected features of abnormal breathing: (1) obstructive or central, (2) apnea or hypopnea, (3) with or without desaturation, (4) with or without irregular breathing, and (5) bradypnea or tachypnea. Upper airway obstruction is determined by the presence of respiratory effort for an apnea, and the presence of inspiratory flow limitation is evidenced by a flattened nasal pressure signal for a hypopnea. Apnea, expressed as “A”, under intravenous sedation is defined by complete cessation of the nasal pressure changes for more than 10 s, whereas hypopnea, expressed as “H”, under intravenous sedation, is defined as being one of three types: H70, H50 and H30. H70 is defined as a more than 70% reduction in the nasal pressure amplitude for more than 10 s. H50 is defined as a more than 50% reduction in the nasal pressure amplitude for more than 10 s. H30 is defined as a more than 30% reduction in the nasal pressure amplitude for more than 10 s. Desaturation, expressed as “D”, is defined as a more than 2% reduction in SpO_2_ for more than 10 s. Irregular breathing, expressed as “I”, is determined when the nasal pressure signal frequency (respiratory rate) and amplitude fluctuate more than twofold after apnea or hypopnea. Irregular breathing is considered to be elicited by laryngeal stimulation with water inside the oral cavity and subsequent cough reflexes. The abnormal breathing index (ABI) is calculated as the number of these abnormal breathing instances per hour of the study period. The abnormal respiratory time (ART) is the duration of one abnormal breathing and is calculated as a mean and a percentage during study period. Similarly, the ABI of apnea (ABI-A) will be used as the primary outcome for a statistical analysis of the study hypotheses.

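### The hypotheses and the 80% power are stated on AHI, but the primary outcome that tests them counts apneas only, and nothing links the two

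*Protocol article*

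**What the plan says.** Section 2.5 frames the formal test on AHI. It says "our null hypothesis is that the mean AHI was not different between intervention A" and intervention B, and that "the alternative hypothesis is that the mean AHI of intervention B is greater than that of intervention A". The planning effect comes from a study of a tongue-stabilizing device in which "Apnea Hypopnea Index (AHI) improved from 21.8 ± 8.6/h to 9.3 ± 5.8/h". Intervention B is taken to be inert: "if intervention B is applied to a participant, there should be no change in AHI". With α of 0.05 and power of 0.80, the section arrives at 9 per intervention, 18 in total, and 26 after allowing for 30% drop-out.

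Section 2.7.1 explains that, because the study runs under sedation, "definitions of apnea and hypopnea as alternatives to AHI and REI that occur during sleep need to be prepared for scoring abnormal breathing". It defines apnea as total loss of the nasal pressure signal lasting over 10 s. It defines three grades of hypopnea (H70, H50, H30) by reductions above 70%, 50% and 30%. It then concludes that "the ABI of apnea (ABI-A) will be used as the primary outcome for a statistical analysis of the study hypotheses". The Abstract also names the apnea index as primary.

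Section 2.7.2 lists ABI-H70, ABI-H50 and ABI-H30 as separate secondary outcomes. The Introduction states the hypothesis more broadly: the two holds "will improve the abnormal breathing events, with superior effects being achieved by the former in OSA patients".

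**The concern.** The variable in the hypothesis and the variable that tests it are different. AHI counts apneas and hypopneas together; ABI-A leaves out every event short of complete cessation. The reasoning in section 2.7.1 supports sedation-specific definitions of both event types. It gives no reason for leaving hypopneas out of the primary outcome, and no section converts the AHI effect into an apnea-only effect.

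Two things are at stake. First, a positive or negative result on ABI-A does not answer the question posed in section 2.5. Second, a reader will take the 80% power as applying to the primary outcome, and it does not. In addition, ABI-A cannot tell a nearly closed airway from an open one, and this matters in a trial that wants to rank two conditions it expects to be at least partly effective.

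**Working it through.** **1. Reproducing the stated sample size.** All effect inputs are AHI figures from section 2.5.

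- Difference: 21.8 − 9.3 = 12.5/h, since B is assumed to leave AHI unchanged.
- SD 8.6/h, so d = 12.5/8.6 = 1.453.
- Two-sample t-test, df = n1 + n2 − 2, two-sided α = 0.05. The noncentrality at 9 per group is 1.453 × √(9/2) = 3.08.
- Power is 0.825 at 9 per group and 0.771 at 8 per group, so n = 9.
- Drop-out: 18/0.7 = 25.7, rounded up to 26.

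The figures 9, 18 and 26 are reproduced. (The one-sided form printed in section 2.5 would give 7 with the same SD. That is a separate matter.)

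**2. What each index counts.** Under the section 2.7.1 definitions, an event lasting over 10 s scores as follows:

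| Event | ABI-A | ABI-H70 | Apnea plus hypopnea |
|---|---|---|---|
| Complete cessation | 1 | separate class | 1 |
| 71-99% reduction | 0 | 1 | 1 |
| Normal flow | 0 | 0 | 0 |

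**3. Direction of the effect on A versus B.** Let r be the event rate with no control, all events being apneas, and c the fraction of them that a hold turns into hypopneas. Both patterns below are assumptions.

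- Pattern 1: B converts a fraction c and leaves the rest; A abolishes all events. The B − A difference is (1 − c)r on ABI-A and r on the combined index.
- Pattern 2: B changes nothing; A converts a fraction c and abolishes the rest. The B − A difference is r on ABI-A and (1 − c)r on the combined index.

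With one event per minute, r = 60/h:

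| | ABI-A | Combined |
|---|---|---|
| Pattern 1, c = 0.5 | 30 | 60 |
| Pattern 1, c = 1 | 0 | 60 |
| Pattern 2, c = 0.5 | 60 | 30 |
| Pattern 2, c = 1 | 60 | 0 |

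The section 2.5 assumption that B leaves AHI unchanged fits both patterns, because B leaves the combined count at r in each. The article therefore does not show which index separates A from B better.

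**4. How far the power could move.** Let f be the ABI-A contrast divided by the 12.5/h AHI contrast. In Pattern 1, f = 1 − c; in Pattern 2, f = 1/(1− c), which is above 1. The article gives no value. The table shows values of f up to 1, using the two-group t-test of step 1:

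| f | Power at 9 per group, SD 8.6 | Power, SD 8.6√f | n per group for 80% (SD 8.6 / SD 8.6√f) |
|---|---|---|---|
| 1 | 0.825 | 0.825 | 9 / 9 |
| 0.75 | 0.584 | 0.708 | 15 / 11 |
| 0.5 | 0.305 | 0.535 | 31 / 16 |
| 0.25 | 0.109 | 0.305 | 120 / 31 |

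With f above 1 and SD 8.6, power at 9 per group would exceed 0.825. These rows show only that the planning figure is sensitive to the choice of index. They are not estimates of this trial's power: section 2.6 records each condition for 1 min (2 min for A if both settings are pooled), so one event already equals 60/h (or 30/h), and an SD from sleep AHI need not carry over.

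**The case against.** The best defence is that ABI-A is openly declared in the Abstract and in section 2.7.1, and that section 2.7.1 deliberately replaces sleep AHI with sedation measures, citing the group's previous report. That stands. There is no doubt about which outcome is primary, and an apnea-only endpoint can be defended. It does not explain why section 2.5 still places the hypotheses and the power on AHI. Nor does the general abnormal breathing index fill the gap: only its component forms are listed as outcomes.

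A reader might infer something stronger: that apnea-only scoring will probably erase the A-versus-B difference, because resting position leaves severe hypopnea while protrusion restores flow. The article does not support this. It says only that both holds should help, with protrusion better, and it gives no conversion fraction. Pattern 2 shows that the combined index can equally be the one that loses the contrast.

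A reader might also infer that converting an apnea to a near-complete hypopnea would pass as a full cure. That is true of the primary score alone. ABI-H70, ABI-H50, ABI-H30, desaturation and event durations are all prespecified secondaries, and the residual event would appear in ABI-H70.

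Finally, eligibility on REI is no evidence of inconsistency. A diagnostic severity criterion need not match the efficacy endpoint.

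**Conclusion.** The mismatch is real and rests on the text alone. Section 2.5 states the hypotheses and the 80% power on AHI, section 2.7.1 tests them on ABI-A, and nothing connects the two. The computed power of 0.825 at 9 per group holds for an AHI difference of 12.5/h with SD 8.6/h; power for ABI-A is not established. Neither the size nor the direction of the consequence for A versus B can be fixed from the article, because both depend on how each hold converts events. The fault is an unreconciled hypothesis and sample size, not a hidden or demonstrably insensitive endpoint. It should be corrected before outcome data are examined.

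**What to change.** Reconcile sections 2.5 and 2.7.1 in one of two ways.

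- **(a) Move the primary outcome to the hypothesis.** Use a sedation index of apneas plus hypopneas, with one hypopnea threshold chosen from the three already defined. Count each event once at its deepest class: the thresholds nest as worded (a reduction above 70% also exceeds 50% and 30%), so adding the indices could double count. Fix this by a dated amendment before any outcome data are examined, and make ABI-A the first secondary outcome.
- **(b) Move the hypothesis to the primary outcome.** Keep ABI-A, restate the null and alternative on it, and either justify an effect size and SD for ABI-A or withdraw the 80% power figure.

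Cost: (a) needs no new measurements, since all event classes are scored from the same traces, but hypopnea scoring is noisier. Section 2.1 opens recruitment on 25 April 2022 and the trial is unblinded, so a change of primary outcome, and the choice among three thresholds, must be reported transparently. Option (b) avoids that and is the less invasive repair. Option (a) aligns hypothesis and outcome but does not rescue the sizing: the sleep-AHI effect and SD would still need justifying for indices counted over 1-2 minutes.

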#### 2.7.2. Secondary Outcome

The ABI of hypopneas (ABI-H70, ABI-H50, ABI-H30), the ABI of desaturation (ABI-D), the ABI of irregular breathing (ABI-I), the mean of ARTs (ART-A ART-H70, ART-50, ART-H30, ART-D, ART-I), and the percentage of ARTs will be used as the secondary outcome for the statistical analysis [20]. The record of OCST, vital signs, electroencephalogram, anesthesia, medical records, questionnaires, and drop-out rate will also be used [21].

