### 2.8. Statistical Analysis

The baseline measures will be compared with the measures obtained under interventions A and B. The normality of data will be tested by the Shapiro–Wilk test. Repeated-measures ANOVA with the Bonferroni correction for multiple testing, followed by Tukey’s honestly significant difference tests will be used as the parametric test for normally distributed data. If the data do not follow a normal distribution, a non-parametric test, the Kruskal–Wallis test with the Bonferroni correction for multiple testing followed by Dunn–Bonferroni tests, will be used. The data will be presented as either the mean ± standard deviation or median (interquartile range) for normal and non-normal distributions. All statistical analyses will be performed using SPSS software (version 25, IBM Japan, Tokyo, Japan). All *p* values are two-tailed and a *p* value of <0.05 is considered to indicate statistical significance.

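### Mean event duration (mean ART) has no value in a 1-min window without an event, so testing it between conditions conditions on a post-treatment result

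*Protocol article*

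**What the plan says.** Section 2.7.1 of the protocol article defines the abnormal respiratory time (ART): it "is the duration of one abnormal breathing and is calculated as a mean and a percentage during study period". Section 2.7.2 then names, as secondary outcomes for the statistical analysis, "the mean of ARTs (ART-A ART-H70, ART-50, ART-H30, ART-D, ART-I", and separately the percentage of ARTs. That makes six mean durations, one per event type.

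Section 2.8 states the comparison: "The baseline measures will be compared with the measures obtained under interventions A and B". The test is repeated-measures ANOVA if the data are normal, and Kruskal–Wallis if they are not.

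Section 2.6 gives the observation time: 1 min at baseline, 1 min under B, and 1 min at each of MAX 50 and MAX 100 under A. By Section 2.7.1, apnea, hypopnea and desaturation count only if they last more than 10 s.

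**The concern.** A mean duration exists only where at least one event occurred. The windows are very short and the device is meant to prevent events, so event-free windows are expected, and under A or B they are the intended result. A participant whose apneas are abolished under A has no mean ART-A for A.

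The set of people who supply a mean ART under a condition is therefore partly decided by that condition. A difference, or lack of one, in mean ART would then describe only those who still had events. It would not describe the randomized participants, and it could rest on very few of them.

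**Working it through.** **Inputs from the protocol article**
- Windows (Section 2.6): 1 min each for baseline and B; 1 min or, if both positions are pooled, 2 min for A. The stated core time confirms this: 0.5 + 1 + 2 + 0.5 + 1 + 1 = 6 min.
- Entry event rate during sleep (Section 2.3.1): 10 to <30/h.
- Planning rates (Section 2.5): AHI "improved from 21.8 ± 8.6/h to 9.3 ± 5.8/h", a ratio of 9.3/21.8 = 0.43.
- Participants (Section 2.5): 18 before dropout; 18/0.70 = 25.7, so 26.

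The article gives no expected event rate under sedation and no figure for event-free windows, so there is no stated value to reproduce for this point.

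**Assumptions:** Poisson counts, windows independent within a person, the same rate for everyone. The rate is varied because it is unknown.

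**Formulas:** P(no event) = exp(−rate × minutes/60). The share with a value in all three conditions is the product of 1 − P(no event) over baseline, A and B.

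**Empty 1-min windows:** exp(−10/60) = 85% at 10/h; 70% at 21.8/h; exp(−30/60) = 61% at 30/h; 37% at 60/h; 14% at 120/h. At the planning rate of 9.3/h it is exp(−0.155) = 86%.

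**Participants with a mean in all three conditions**

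| Baseline rate | No effect, A 1 min | No effect, A 2 min | A at ratio 0.43, A 1 min | A at ratio 0.43, A 2 min |
|---|---|---|---|---|
| 10/h | 0.4% | 0.7% | 0.2% | 0.3% |
| 21.8/h | 2.8% | 4.8% | 1.3% | 2.5% |
| 30/h | 6.1% | 9.8% | 3.0% | 5.4% |
| 60/h | 25% | 35% | 14% | 23% |
| 120/h | 65% | 73% | 43% | 61% |

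Worked example at 30/h with no effect: 0.393 × 0.393 × 0.393 = 0.061, which is 1.6 of 26. At the planning rates with A pooled over 2 min: 0.305 × 0.305 × 0.267 = 0.025, which is 0.4 of 18.

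More than half of participants are retained only above about 95/h (no effect) or 137/h (ratio 0.43) with 1-min windows. With A pooled over 2 min, the thresholds are about 79/h and 100/h.

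**Sensitivity to a common rate.** Letting rates vary between people (gamma, coefficient of variation 0.5) changes the no-effect, 1-min figures from 2.8% to 3.9% at 21.8/h, from 25% to 26% at 60/h, and from 65% to 57% at 120/h.

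**Dependence on response (illustration only).** Suppose half the participants have 80% fewer events under A and the rest have no change, with 1-min windows and the same gamma variation. By simulation, complete cases are 8% of responders and 26% of non-responders at 60/h, and 24% and 57% at 120/h. Someone with no event under A is always lost from the complete cases.

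**Entering zero instead.** If events last d on average under every condition, the zero-filled mean has expectation P(at least one event) × d. At 21.8/h and 9.3/h in 1-min windows the ratio of A to baseline is 0.144/0.305 = 0.47, although no event became shorter. Pooling A over 2 min moves it to 0.267/0.305, about 0.87. The result reflects occurrence and window length, not duration.

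**The case against.** Several objections have force.

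- **The rate is unknown.** The cited rates are AHI and REI during sleep. Section 2.7.1 says sedation needs its own definitions, and the Discussion says that propofol can suppress upper airway muscle activity more than natural sleep does. Rates could be much higher, at least for a frequent type such as H30. A reader might infer that most participants will be dropped. The documents do not support that as a fact: it holds at the rates they cite and fails above the thresholds shown. Conversely, the cited rates combine event types, so at the same overall rate apnea alone would be rarer.
- **ANOVA is only one branch.** Loss of whole participants follows from repeated-measures ANOVA. Kruskal–Wallis does not need a value in every condition, so the complete-case percentages do not apply to it. The selection remains, because event-free windows still drop out.
- **Much of the loss is not due to response.** At the planning rates, baseline and B alone leave 0.305 × 0.305 = 9.3%. Sparse events account for most of the loss before A is considered.
- **A reader might also infer bias toward no effect.** This is not shown. The calculations model how often events occur, not how long they last. If frequency response and duration are unrelated, keeping mainly frequency non-responders need not distort mean duration. The responder split and the 80% reduction are also assumptions.
- **A convention may sit in the full protocol or analysis plan.** That is possible, and its absence from an article is no fault. The point does not rest on it: omitting event-free windows selects on outcome, and entering zero changes what is measured.

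**Conclusion.** The point holds in a limited form. As fixed in Sections 2.6 to 2.8, mean ART is undefined in event-free windows, and comparing it between conditions conditions on a post-treatment result. That needs no assumed rate.

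The extent of the loss does need one. Under the Poisson assumption and at the entry rates, at most about 6% of participants (about 10% with A pooled over 2 min) would have all three values. At 120/h, 43–65% would be retained with 1-min windows, and 61% with the planning effect and A pooled over 2 min. Size and direction of any bias in mean duration are not established.

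The consequence is confined to six secondary outcomes. The primary outcome, ABI-A, and the percentage of ART both take a valid zero when no event occurs.

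**What to change.** In Section 2.7.2, make the percentage of ART the tested duration outcome for each event type, with zero where no event occurs. Report mean ART only descriptively, among windows with at least one event, giving the number of participants and windows that contribute under each condition, and without a between-condition test.

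This is a change of wording and needs no new data. The cost is six fewer tested secondary variables: whether the events that still occur are shorter would be described but not tested.
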